#### Treatment of the control group

The supervisors in the control group did not receive training. If the intervention 'Staying healthy at work' proves to be effective, the supervisors in the control group will be trained in the future. Workers in the control group are being given CAU, which implies no structured support, but the possibility of counselling or support by HRPs or other professionals as required, or participating in training and human resource tools.

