### Effect evaluation

To investigate the effectiveness of the intervention 'Staying healthy at work', all workers received a baseline questionnaire, and follow-up questionnaires are to be filled in at 3, 6 and 12 months.

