### Primary outcome

The primary outcomes of the study are: work ability, vitality and productivity.

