#### Vitality

Improvements in health-related outcomes are being evaluated with the self-reported 12-Item Short Form Health Survey (SF-12), an abbreviated version of the 36-Item Short Form Health Survey [34-36]. The SF-12 provides two summary scores, the Physical Component Summary (PCS) score, which represents what a person can do, and the Mental Component Summary (MCS) score, which represents how a person feels. The mean PCS and MCS of the general population are 50, with a standard deviation of 10. A higher score means a better quality of life.

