#### Productivity

Productivity is being measured with the QQ method, which aims at measuring the quantity and quality of work performed on a daily basis [37]. The workers indicate how much work they actually perform during regular hours on their last regular work day during a working week as compared with a normal week day. The quantity of productivity is measured on a 10-point rating scale with 0 representing 'nothing' and 10 representing 'normal quantity'. Meerdings et al. [9] showed that self-reported productivity in the QQ measurement correlated significantly with objective work output.

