### Statistical analyses

All analyses will be performed according to the intention-to-treat principle. Baseline characteristics of workers will be analyzed for differences between the intervention and the control groups. Differences between the intervention and the control groups in changes on the outcome variables will be performed with multi-level longitudinal analysis. Intra-cluster correlations will be determined for all primary outcome variables. Effects of the intervention will be controlled with covariates, such as gender and job type. Further analyses will include the comparison of the secondary outcomes at follow-up between the two arms. For all analyses a two-tailed significance level of p < 0.05 is considered to be statistically significant. All analyses will be carried out with the statistical package SPSS version 16.0 (SPSS Inc. Chicago, IL, USA).

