### Power calculations and sample size

Work ability, measured with the Work Ability Index (WAI) [46] is the primary outcome measure for the power calculation. The range of the summative index of the WAI is 7-49, which is classified into four subgroups: poor (7-27), moderate (28-36), good (37-43), and excellent (44-49) [31]. The target of this intervention study is to increase the mean scores of the workers to those of the next subgroup. This implies a minimum increase of 5.4 (24%) for workers with a poor work ability, and minimum increase of 3.7 (11% and 9%, respectively) for workers with a moderate and good work ability before the intervention. For the workers with an excellent WAI score at baseline, the aim is to maintain the score. The survey study demonstrates that the effect size of workers is high (≥0.80).

We used Optimal Design [47,48] to calculate the optimal sample size by a power of 0.80 for testing the treatment effect in this cluster-randomized trial with an intervention and a control group in a repeated measurement design. A literature search on the role of the supervisor to the worker's attitude [24,49] showed an intra-class correlation (ICC) between 0.11 and 0.26 for supervisors. We used the most extreme value (ICC = 0.26) for the power calculation. A total of 20 supervisors are enough to reach a power of 80%.

Calculating from 80% power (two-sided, alpha = 0.05, 20 supervisors) a sample size of eight workers per supervisor are needed to determine a significant difference between the intervention and the control groups. The eight workers must be viewed as the average number of workers per supervisor. This requires at least 80 workers in each group. Allowing for a loss to follow-up of 15%, a sample size of 92 workers (in each group) is required.

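### Three equal primary outcomes, only one of them powered, share an unadjusted 0.05 with no success rule; if any one suffices, the false-claim rate is roughly 10–19%, not 5%

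*Protocol article*

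**What the plan says.** - **Primary outcome:** "The primary outcomes of the study are: work ability, vitality and productivity". The abstract and the stated aim in the Background list the same three in different orders, so no ranking can be read from the order.
- **Vitality:** "The SF-12 provides two summary scores", physical (PCS) and mental (MCS). Neither is chosen as the vitality endpoint.
- **Productivity:** "The quantity of productivity is measured on a 10-point rating scale". The QQ method is described as covering quality as well, but no rating for quality is given.
- **Effect evaluation:** "follow-up questionnaires are to be filled in at 3, 6 and 12 months". No primary time point is named.
- **Statistical analyses:** group differences in change are to be assessed by a multilevel longitudinal analysis. On the threshold: "For all analyses a two-tailed significance level of p < 0.05 is considered to be statistically significant". No adjustment or order of testing accompanies this.
- **Power calculations and sample size:** the WAI "is the primary outcome measure for the power calculation". No other outcome is powered.
- **Treatment of the control group:** "If the intervention 'Staying healthy at work' proves to be effective, the supervisors in the control group will be trained in the future". What would prove effectiveness is not defined.

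**The concern.** With several outcomes of equal standing and one unadjusted threshold, the error rate of the overall conclusion depends on how the results are combined. The article does not say how. If one significant primary outcome is enough, the 5% level does not describe the risk of a false claim of effectiveness. If all are required, the false-claim risk is controlled, but the sample size was never shown to support that claim. Because the rule is open, it could be settled after the results are known. The conclusion also has a stated consequence, the later training of supervisors in the control group.

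**Working it through.** **Inputs from the article.** Three primary outcomes, or four scores if both SF-12 summaries are tested. Two-sided alpha 0.05. Power inputs: effect size 0.80 (stated as at least 0.80), intra-class correlation 0.26, 20 supervisors, 8 workers each.

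**Assumed inputs.** The article gives no correlations between outcomes or visits. Those below are assumptions, shown as ranges.

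**Step 1: reproduce the stated power for the WAI.**
- SE = sqrt(4 × (0.26 + 0.74/8) / 20) = sqrt(4 × 0.3525 / 20) = sqrt(0.0705) = 0.266 standard deviations.
- Noncentrality = 0.80 / 0.266 = 3.01.
- Power from the noncentral t with 18 degrees of freedom is 81.3%; a normal approximation gives 85.4%.

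The stated 80% is therefore reproduced, for one outcome tested once at 0.05.

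**Step 2: any one primary outcome suffices.** Chance of at least one false positive when there is no effect on any outcome:

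| Correlation between test statistics | 3 outcomes | 4 scores |
|---|---|---|
| 0 (1 − 0.95^k) | 14.3% | 18.5% |
| 0.3 (simulated) | 13.6% | 17.4% |
| 0.5 (simulated) | 12.5% | 15.6% |
| 0.8 (simulated) | 9.8% | 11.4% |

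Even the most favourable entry is about twice the nominal 5%.

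**Step 3: all primary outcomes must be significant.** The chance of a false joint claim cannot exceed 5%. With no effect anywhere it was 1.4% or less in the same simulations. Power is the difficulty. Suppose every outcome had the WAI's 81.3% power and the tests were independent. Joint power would then be 0.813^3 = 54% for three outcomes and 0.813^4 = 44% for four scores. Positive correlation raises this, to 81.3% at most. Outcomes with smaller effects lower it.

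**Step 4: upper scenario, four scores each tested at three visits.** Twelve tests give 46.0% if independent. With assumed correlations of 0 to 0.7 between outcomes and 0.5 to 0.8 between visits, the simulated values run from about 24% to 40%. The article does not state this analysis.

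**Step 5: cost of splitting alpha instead.** Under Bonferroni with 20 supervisors of 8 workers, WAI power falls from 81.3% to 64.7% for three outcomes (alpha 0.0167) and to 60.0% for four scores (alpha 0.0125). About 28 supervisors would be needed to return to at least 80% (83.4% and 80.3%).

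**The case against.** **Visit-by-visit testing.** A reader might infer from three follow-ups and one threshold that each score will be tested at each visit, and quote 24–40% as the trial's error rate. The article does not support this. It schedules the questionnaires and plans a longitudinal model, which may give one treatment test per score. What stands is narrower: no contrast or time point is named, so repeated testing is not ruled out.

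**Any-one rule.** A reader might also take it as settled that one significant outcome means effective. The article never says so; the wording on training control supervisors leaves the criterion open. The inflation is therefore conditional.

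**Independence is a worst case.** All three outcomes are self-reported by the same worker. The WAI also covers disease, impairment and psychological resources, so overlap with the SF-12 is likely. This objection stands, which is why the correlated range is given. It reduces the inflation but does not remove it. Four tests also presuppose that both SF-12 summaries are tested as primary.

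**Details left to an analysis plan.** Success rules and multiplicity procedures are often placed in a document not shown here, and powering on one of several primary outcomes is ordinary practice. The article is not merely silent, however. It sets one unadjusted level for every analysis, and a multiplicity rule elsewhere would have to be reconciled with that sentence.

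**Changing the hierarchy is not mere wording.** The trial is registered, workers are enrolled and baseline data are collected. This stands, and it is counted in the cost of the fix.

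**Conclusion.** The point holds in conditional form. Three equal primary outcomes, a single powered outcome, no success rule and an unadjusted level fixed for all analyses leave the error rate of the main conclusion undefined. If any one primary outcome suffices, it is 14.3% or 18.5% under independence and about 10–17% under assumed correlations of 0.3 to 0.8. If all must succeed, it is below 5%, but the trial has no stated power for that claim. Higher figures apply only if every visit were tested separately, which the article does not say. This should be fixed before analysis. It does not invalidate the design, and the WAI power figure itself is sound on its stated inputs.

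**What to change.** 1. Name one treatment contrast per score from the planned multilevel longitudinal model, for example the group difference in change at 12 months. Check the power statement for that contrast, since the calculation was made for a repeated-measurement design.
2. Test the WAI first at two-sided 0.05.
3. Only if the WAI is significant, test PCS, MCS and QQ productivity with Holm (smallest p-value against 0.05/3 = 0.0167, then 0.025, then 0.05).
4. Report other time points and the secondary outcomes as exploratory, and replace the sentence on the threshold accordingly.

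This holds the family-wise error at 5%. If the WAI has no true effect, any false claim must first pass its 5% test. If it has one, Holm protects the other three. State also that the QQ score is the quantity rating, or add the quality rating to the Holm set.

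**Cost.** No additional supervisors or workers, subject to the check in item 1. There would be no confirmatory claim on vitality or productivity if the WAI test fails. Ordering the declared primary outcomes is a change of substance and must be recorded in the protocol and the registration before analysis. A fixed sequence through all the scores starting with the WAI, or an explicit rule that all must succeed, would also control the error; the latter would need its own power calculation.

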### Power calculations and sample size

Work ability, measured with the Work Ability Index (WAI) [46] is the primary outcome measure for the power calculation. The range of the summative index of the WAI is 7-49, which is classified into four subgroups: poor (7-27), moderate (28-36), good (37-43), and excellent (44-49) [31]. The target of this intervention study is to increase the mean scores of the workers to those of the next subgroup. This implies a minimum increase of 5.4 (24%) for workers with a poor work ability, and minimum increase of 3.7 (11% and 9%, respectively) for workers with a moderate and good work ability before the intervention. For the workers with an excellent WAI score at baseline, the aim is to maintain the score. The survey study demonstrates that the effect size of workers is high (≥0.80).

We used Optimal Design [47,48] to calculate the optimal sample size by a power of 0.80 for testing the treatment effect in this cluster-randomized trial with an intervention and a control group in a repeated measurement design. A literature search on the role of the supervisor to the worker's attitude [24,49] showed an intra-class correlation (ICC) between 0.11 and 0.26 for supervisors. We used the most extreme value (ICC = 0.26) for the power calculation. A total of 20 supervisors are enough to reach a power of 80%.

Calculating from 80% power (two-sided, alpha = 0.05, 20 supervisors) a sample size of eight workers per supervisor are needed to determine a significant difference between the intervention and the control groups. The eight workers must be viewed as the average number of workers per supervisor. This requires at least 80 workers in each group. Allowing for a loss to follow-up of 15%, a sample size of 92 workers (in each group) is required.

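### The 15% loss allowance was added to 80 rather than divided out: 92 workers per group leave about 78, not the 80 required; the figure should be 95

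*Protocol article*

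**What the plan says.** The section *Power calculations and sample size* of the protocol article builds the sample size in three steps.

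- Cluster size: "Calculating from 80% power (two-sided, alpha = 0.05, 20 supervisors) a sample size of eight workers per supervisor are needed". The text adds that "The eight workers must be viewed as the average number of workers per supervisor".
- Minimum per group: "This requires at least 80 workers in each group".
- Loss to follow-up: "Allowing for a loss to follow-up of 15%, a sample size of 92 workers (in each group) is required".

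The article gives no formula for the last step and no other reason for 92. The other inputs in the section are the intra-class correlation ("We used the most extreme value (ICC = 0.26) for the power calculation") and the effect size ("The survey study demonstrates that the effect size of workers is high (≥0.80").

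**The concern.** The second and third steps do not fit together. If 80 per group is the number needed after losses, and 15% of those enrolled are lost, then enrolling 92 does not leave 80. The pattern is a familiar slip: the target is multiplied by one plus the loss rate, when it should be divided by one minus the loss rate.

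At stake is a headline design figure against which enrolment and attrition will later be judged. As written, the trial could meet its enrolment target, lose exactly the share it planned for, and still finish below its own stated minimum.

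**Working it through.** **Inputs**, all from *Power calculations and sample size*:

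- 20 supervisors, on average 8 workers each, two groups
- loss to follow-up 15%
- stated size 92 per group
- two-sided alpha 0.05, target power 80%
- intra-class correlation (ICC) 0.26
- effect size at least 0.80; the value 0.80 is taken for the power check, as an assumption

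**1. The minimum.** 20 × 8 / 2 = 80 per group. This is the output of the power calculation before any allowance for loss, so it is the number needed after loss.

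**2. Reproducing the plan's figure.** 80 × (1 + 0.15) = 92.0. The match is exact, with no rounding.

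**3. What 92 delivers.** 92 × (1 − 0.15) = 78.2 per group, about 2 below the minimum. The largest loss that still leaves 80 is 1 − 80/92 = 12/92 = 13.0%.

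**4. The correct inflation.** n / (1 − loss) = 80 / 0.85 = 94.12, rounded up to 95.

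| Enrolled per group | Left after 15% loss | Meets 80? |
|---|---|---|
| 92 | 78.2 | no |
| 94 | 79.9 | no, just short |
| 95 | 80.75 | yes |

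The total is 2 × 95 = 190, against 2 × 92 = 184. Inflating the total in one step gives 160 / 0.85 = 188.2, so 189.

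**5. Effect on power.** For K supervisors in total and m workers per supervisor, a two-sided t-test on K − 2 = 18 degrees of freedom has noncentrality

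d / (2 × √[(ICC + (1 − ICC)/m) / K]).

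- m = 8: (0.26 + 0.74/8) / 20 = 0.017625; noncentrality 0.80 / (2 × 0.1328) = 3.01; power 0.813.
- m = 7.82 (78.2 workers over 10 supervisors): noncentrality 3.00; power 0.811.
- m = 7: noncentrality 2.96; power 0.799.

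Eight is thus the smallest whole number per supervisor that reaches 80% under this model, which agrees with reading 80 per group as a minimum. The model is a simple two-level comparison. It does not reproduce the repeated-measures calculation that the article says was done in Optimal Design, whose full inputs are not given.

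**The case against.** The strongest case on the other side accepts the arithmetic and disputes its importance. It has four parts.

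- **Power is not threatened.** Under the inputs above, power stays at 0.80 down to about 7.1 workers per supervisor, or about 71 per group. Against the power target, 92 enrolled could bear a loss of roughly 23% (1 − 71/92). This stands, given an effect size of 0.80. The 13% limit applies to the stated minimum of 80, not to the power that the minimum serves.
- **Eight is an average.** A mean of 7.8 rounds to eight, and 92 differs from the unrounded 94.12 by only 2.3%. This is fair as a comment on size, but the article also calls 80 a minimum, and that minimum is missed.
- **Partial data may be used.** "Statistical analyses" plans an intention-to-treat, multi-level longitudinal analysis, with follow-up at 3, 6 and 12 months. A worker lost after the 3-month or 6-month questionnaire can still contribute, so 78 is best described as the number with complete follow-up. This softens the effect. The article does not say how partial data will be handled, and the point does not explain 92.
- **Recruitment appears to be over.** The article describes enrolment and baseline measurement in the past tense, so adding workers may no longer be possible. That bears on which correction to choose, not on whether one is needed.

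None of this makes 92 the right answer to the calculation that the article describes.

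**Conclusion.** The concern holds. Under the plan's own 15% loss, 92 per group falls short of the plan's own minimum of 80, and the cause is an allowance added instead of divided out. The size is small: 3 workers per group, 6 in total, and about 0.2 percentage points of power, which stays above 80%. Severity is low, and this is not a finding that the trial is underpowered.

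The arithmetic rests only on reading 15% as a share of those enrolled and 80 as the number required after loss. The statement about power rests in addition on an effect size of exactly 0.80 and on the simple two-level model.

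**What to change.** Replace 92 with 95 workers per group (190 in total) and show the step as 80 / 0.85.

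If enrolment has closed at 92 per group, keep that number and restate what it provides, in one of two ways:

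- 92 per group allows for a loss of 13%; or
- 92 per group leaves about 78 per group (7.8 per supervisor) with complete follow-up after a 15% loss, with the power recomputed for that number by the method used in the original calculation.

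Either restatement changes one sentence and needs no added recruitment. The first option needs 3 more workers per group. Neither route alters the design or the analysis.

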### Blinding

The validity of the study will be compromised if information is known about the intervention in the control group. To minimize data contamination, pre-randomization at the supervisor level is applied for allocating the workers into the intervention or the control group. Therefore, different information about the study can be provided to workers in the intervention and the control groups [27]. Workers in the control group do not know the content and design of the intervention 'Staying healthy at work'. Whereas workers in the control group are blinded to the intervention, blinding of the supervisors was not possible. Supervisors in the control and the intervention groups have been informed about the content of the intervention, because they already knew the set-up of the study prior to their decision to participate.

## Discussion

The results of this cluster-randomized controlled study will provide input for an evidence-based intervention which may improve a sustainable healthy working life of workers aged 45 years and older. The intervention offers a structured method for workers to communicate with their supervisor about their work environment, barriers to work performance and career opportunities. Aspects concerning intervention procedure are described in the protocol; however, supervisors and workers are free to choose specific tools at each phase of the process. We assume that such a structured (non-protocol) intervention strategy giving workers the opportunity to make an action plan for the next 1-year follow-up period, will be an effective way to create a sustainable, healthy, working life for older workers. Moreover, this method has been shown to be effective in shortening sick-leave duration by workers on their first sick leave [50].

### Strengths

One of the main strengths of the intervention 'Staying healthy at work' is that it offers a strategy to improve the problem-solving capacity of both workers and supervisors. The workers will be trained to be aware of their own decisive role in attaining goals, and they will learn how to cope with future problems related to work participation. The skills of the supervisors will be improved by strengthening the workers' ability to act and make decisions autonomously, and to not take over the workers' responsibilities. Additional value of the intervention is that the method will contribute to the annual assessment, between supervisor and worker, of work functioning and participation. The intervention method can be incorporated into the annual worker assessments within the organization. Another strength of the intervention is the close cooperation with the HRPs during the development of the intervention. This offers a tool and a process that fit in with the existing company policy and improves the likelihood of effectiveness of the intervention. Furthermore, the intervention will contribute to the knowledge and the use of the current tools, education and training within the organization to enhance work participation. Although many organizations have these tools available in their current policy, supervisors and workers are often unaware of the opportunities they have aimed at improving the working environment. The fact that the perspectives of the workers on work functioning will be taken into account is also a strength of this study. We presume that this will lead to a better compliance of the workers to participate actively in the intervention programme. This will improve the effectiveness of the study. Finally, the cluster design of the study reduces the risk of data contamination between workers in the intervention and the control groups. Supervisors are randomly assigned to the intervention or the control group. Pre-randomization enables workers in the intervention group to be informed separately, and therefore makes it possible to blind the workers in the control group to the study condition.

